#### Implementation {16c}

The selection and assignment randomisations will be carried out by an external SIDIAP data manager. The researchers will contact the PCT managers to inform them. If managers agree to participate, a pair of researchers will attend the PCT and if 60% of the PCT professionals agree, they will be randomly assigned to the IG or the CG prior to the presentation session.

### Assignment of interventions: blinding

#### Who will be blinded {17a}

Not applicable due to the characteristics of the study, even the data analysis will be open-label.

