#### Intervention description {11a}

VERTAP clinical trial (training intervention to improve the management of vertigo in primary care).

The objective of this protocol is to evaluate the efficacy of blended online and face-to-face training on the diagnosis and treatment of vertigo, in order to improve the adherence of family doctors to clinical practice guidelines.

Using the CAMFiC Moodle platform, we will adapt a pre-existing course prepared by the VERTAP that will contain videos showing the main diagnostic and therapeutic manoeuvres for vertigo. The contents will be reviewed by family doctors, physiotherapists and an ENT specialist. It will conform to the objectives of the study, with interactive clinical cases to improve the diagnosis and treatment of patients with vertigo. The online course requires approximately 14 h of individual study. This course will have to be completed within 6 weeks from the moment of registration and access.

After training with ENT and vestibular rehabilitation specialists, medical researchers will conduct the face-to-face session to verify and discuss the correct performance of the manoeuvres. The face-to-face group session lasts approximately 90 min. It will be carried out by a pair of researchers going to the PCT, who will supervise each doctor’s implementation of the diagnostic and therapeutic manoeuvres learned in the online course. During this session, researchers will also standardise the diagnosis and management of vertigo. Once the study period is over, the CG will be offered the possibility of taking the course.

An online course follow-up team will send email reminders regarding the start, follow-up and completion of the course. VERTAP researchers will take the register in the face-to-face sessions.

The TIDieR checklist will be followed during the intervention.

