	***Study period***					
	Enrollment	Allocation	Post-allocation			Follow-ups
**Time point**^**a**^	t1		t2	t3	t4	t1–t4
**Enrollment**	x					x
**Eligibility screen**	x					x
**Presentation of the study**			x			x
**Allocation**	x					x
**Interventions**			x			x
**Online training**			x			x
**Face-to-face session**			x			x
**Assessments**				x		x
**Period of information collection**				x	x	x
**Analysis of results**					x	x
**Dissemination of the results**						x

^a^List specific time points: *t1* November 2019 to August 2021, *t2* September 2021 to March 2022, *t3* January 2022 to December 2022, *t4* January 2023 to December 2023

This phase will start in November 2019 and last until March 2021 (this period was extended to May 2021 due to the COVID 19 pandemic). The VERTAP team will meet with the ENT specialist once monthly.

The SIDIAP will randomise the participating centres and assist in defining the study variables.Phase 2: Presentation of the study to 20 PCT in the Southern Metropolitan Area of the Catalan Institute of Health from June to September 2021—participating PCT will be randomly assigned to the IG or the CG.

The IG will start the course at the beginning of the study, and PCT in the CG will start the training after the study follow-up period has ended.

The PCT in the IG will access the course online platform during November and December 2021. The face-to-face sessions will take place from January to April 2022.Phase 3: The period of information collection will be extended to January 2022 to December 2022.Phase 4: Analysis of results—data will be analysed by the researchers and a statistician. Manuscript writing will last from January to March 2023. The results will be published in scientific journals and disseminated in national and international conferences.

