### Data collection and management

#### Plans for assessment and collection of outcomes {18a}

The IG PCT will receive online and face-to-face training on the diagnosis and treatment of vertigo in general and of BPPV in particular, and also on the correct ICD-10 diagnostic codes. After the completion of the study, the CG PCT will be offered the same training. All data will be extracted from the SIDIAP pseudonymised database, a research platform that includes the computerised primary care medical records of 80% of the Catalan population.

Primary outcome: improvement in the specific and non-specific diagnoses of vertigo. Secondary outcome: comparison between the IG and CG of percentage of patients treated with antivertigo agents, and percentage of referrals to neurology and ENT.

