#### Data management {19}

Clinical trial data will be entered electronically. Variables will be extracted from the SIDIAP before starting the training and quarterly during the 12 months after the start of the trial. The data of all patients with a new diagnosis of vertigo and dizziness in participating centres will also be collected, ensuring a sample size greater than necessary. The files will be safely stored in numerical order in one location for a period of 3 years after the end of the study. Only SIDIAP staff will be able to export these data.

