### Oversight and monitoring

The management structure comprises the principal investigator (IP), VERTAP members and a collaborating centre that will manage the data.

The VERTAP members are responsible for conducting the clinical trial. They will meet monthly to discuss the progress of the trial. During these meetings, the PI will verify that the study objectives are being met according to schedule.

The VERTAP constitutes the Steering Committee. They will periodically review the progress of the study.

The statistic analysis will be performed by the database research centre and the VERTAP statistician. Additional follow-up may be performed at the discretion of the monitoring manager.

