### Composition of the data monitoring committee, its role and reporting structure {21a}

Since the original SIDIAP database is external to the study, and the data is obtained at two specific moments in time through computerised extraction; there is no role in this study for a data monitoring committee. The SIDIAP, [name] and [name] will be responsible for data extraction.

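### The plan makes the analysis open-label for a reason that covers only the GPs and trainers, although its own data flow would allow a masked analyst

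*Protocol article*

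**What the plan says.** Who will be blinded {17a} reads: "Not applicable due to the characteristics of the study, even the data analysis will be open-label". No other reason is given.

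The relevant data flow is described elsewhere in the protocol:

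- **Allocation.** Implementation {16c}: "The selection and assignment randomisations will be carried out by an external SIDIAP data manager".
- **Source of outcomes.** Plans for assessment and collection of outcomes {18a}: "All data will be extracted from the SIDIAP pseudonymised database". The data monitoring section {21a} adds that "the data is obtained at two specific moments in time through computerised extraction".
- **Release of data.** Data management {19}: "Only SIDIAP staff will be able to export these data".
- **Who analyses.** Participant timeline {13}, Phase 4: "data will be analysed by the researchers and a statistician". Oversight and monitoring: "The statistic analysis will be performed by the database research centre and the VERTAP statistician".
- **Who trains.** Intervention description {11a}, on the face-to-face session: "It will be carried out by a pair of researchers going to the PCT".

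The steering committee consists only of members of the trial group, and the protocol sees no role for a data monitoring committee.

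**The concern.** Masking is not all-or-nothing. GPs know whether they have been trained and trainers know whom they trained, but the person who runs the models need not know which arm is which. The protocol extends the open-label status to the analysis and supports this with a reason that applies only to the GPs and trainers.

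This is a stated decision, not a detail left to a fuller document. It matters because the people who may analyse include those who built and delivered the course, there is no outside check on the analysis, and some choices are unsettled in the text. With arms visible, such a choice can be made after seeing which option favours the training, even without intent.

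**Working it through.** The protocol gives no figure on this point, so there is none to reproduce. The check has three steps.

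**1. Can the analyst be masked under the plan's own arrangements?**

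| Requirement | What the protocol provides |
|---|---|
| Allocation generated outside the research team | Yes: external SIDIAP data manager ({16c}) |
| Outcomes obtained without a trial assessor who knows the arm | Yes: computerised extraction from a pseudonymised database ({18a}, {21a}) |
| A single gate where labels can be recoded | Yes: export by SIDIAP staff only ({19}) |
| Key-holder separate from analyst | Not assured: the database research centre also shares in the analysis (Oversight and monitoring) |

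Three of the four conditions are met. The fourth needs a separation of roles. Team identifiers must be recoded as well as arms, because the researchers know which teams they visited.

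**2. Which choices are unsettled in the text shown?**

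- *Outcome window.* Trial design {8} counts the year from completion of training in each team. Outcomes {12} counts a year from the start of training. Study setting {9} gives January to December 2022. Online access runs November to December 2021 and face-to-face sessions January to April 2022 ({13}). A year from a November 2021 start ends around October 2022; a year from an April 2022 completion ends around April 2023. These two windows share only about half their months. The first and the calendar year 2022 share about ten of twelve.
- *Diagnoses counted as specific.* Outcomes {12} names BPPV, Menière's and vestibular neuritis. Sample size {14} adds vestibular migraine. The full list is in Supplementary material 1, which is not shown and may settle this.
- *Ratio or proportion.* {12} uses both. With p the proportion specific, the ratio is p/(1 − p), which rises whenever p rises, so this is nearly one analysis. In a simulation of null t-tests on 10 against 10 centres (assumed p = 0.30, ICC 0.05, 200 patients per centre) the two statistics correlated about 0.98, and taking the better gave about 5.5% error. It adds almost nothing.

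**3. What could choosing the better of two analyses do?**

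Assume two standard normal test statistics Z₁ and Z₂ under the null, with correlation r. The documents do not give r.

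- Two-sided: error = 1 − P(|Z₁| < 1.96 and |Z₂| < 1.96).
- In favour of training only: error = 1 − P(Z₁ < 1.96 and Z₂ < 1.96).

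| Assumed r | Two-sided (nominal 5%) | Favouring training (nominal 2.5%) |
|---|---|---|
| 0.5 | 9.1% | 4.5% |
| 0.7 | 8.3% | 4.2% |
| 0.9 | 7.0% | 3.5% |

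The right-hand column matches the harm described, which runs in one direction. Overlapping windows in the same teams would be expected to correlate strongly, so the bottom row is the more plausible end.

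**The case against.** The best case against the point has five parts.

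*The open-label status is disclosed and the outcomes are automated routine records.* True. Automation removes assessor bias at extraction, but it does not touch choices made at the analysis stage, and disclosure is not a justification.

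*Few choices are really open.* Largely right. A reader might infer that the outcome test is also open between t-test and Mann-Whitney. Statistical methods {20a} does not support that: the pair is listed for baseline variables, and the t-test is named for outcomes. A reader might then count four open analyses and arrive at an error of 9 to 16%. That needs four distinct analyses, which the text does not show: the test is stated, ratio and proportion nearly coincide, and the code list may be settled in the supplement. The window is the one choice clearly unsettled.

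*An unsettled window is cured by reconciling the passages and fixing the choice in advance, possibly in an analysis plan not shown.* Agreed that prior specification does most of the work, so the fix puts it first. Masking protects whatever judgement remains after that.

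*Masking is neither free nor complete.* This stands. The key-holder must be kept apart from the analyst. Simply stripping training dates would stop the analyst from building a window that depends on them. If specific diagnoses rise from 30% to 40% as {14} expects, the arms might be guessed.

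*The larger bias is elsewhere.* Also true. Trained GPs record the outcome codes themselves and are taught correct ICD-10 coding ({18a}). Masking the analyst leaves that untouched.

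**Conclusion.** The point holds as a modest, avoidable weakness. {17a} rules out masking of the analysis for a reason that does not reach the analysis, while the protocol's own allocation and export arrangements make a masked analyst practicable. The exposure is real because researchers who deliver the training may share in the analysis, oversight is internal, and the outcome window is described in three ways.

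The documents do not give its size. The 7 to 9% two-sided range, or 3.5 to 4.5% in favour of training, rests on two assumptions: that two distinct analyses are available, and that their correlation lies between 0.5 and 0.9. It is an illustration and not an estimate for this trial.

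Nothing in the protocol shows that any choice has been or will be made to favour the training, and a reader should not infer that. Nor should a reader infer that masking the analyst would make the primary outcome free of bias. Sample size, alpha and power are unaffected.

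**What to change.** Replace the sentence in {17a} with text to this effect:

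1. GPs and trainers are unmasked.
2. The outcome window, the list of specific and nonspecific codes, and the model are fixed in writing before any data are released. This includes reconciling the window in {8}, {9} and {12}, and the diagnoses in {12} and {14}.
3. SIDIAP derives each team's outcome window, so that training dates need not reach the analyst, and delivers the analysis file with recoded team identifiers and arms labelled A and B.
4. The statistician runs the primary and secondary analyses on this file.
5. The key is held by a SIDIAP data manager who takes no part in the analysis, and is released after the results are locked.

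If this is not possible, {17a} should say why.

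The cost is small: one relabelling and window-derivation step at SIDIAP and a separation of existing roles. Masking may be imperfect if the shift in coding reveals the arm, which is why item 2 must come before data release.

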#### Procedure for unblinding if needed {17b}

Not applicable due to the characteristics of the study.

### Data collection and management

#### Plans for assessment and collection of outcomes {18a}

The IG PCT will receive online and face-to-face training on the diagnosis and treatment of vertigo in general and of BPPV in particular, and also on the correct ICD-10 diagnostic codes. After the completion of the study, the CG PCT will be offered the same training. All data will be extracted from the SIDIAP pseudonymised database, a research platform that includes the computerised primary care medical records of 80% of the Catalan population.

Primary outcome: improvement in the specific and non-specific diagnoses of vertigo. Secondary outcome: comparison between the IG and CG of percentage of patients treated with antivertigo agents, and percentage of referrals to neurology and ENT.

#### Plans to promote participant retention and complete follow-up {18b}

After randomisation, the IG will make every reasonable effort to complete the study. The anticipated annual loss-to-follow-up is ≤ 5%. Physicians in the IG should commit to take the online and face-to-face course and apply the procedures learned during the study.

The PCT of Catalonia are currently focused on the COVID-19 pandemic. However, it is expected that PCT will resume normal primary care activities shortly. To increase adherence to the online course, participants will receive a weekly email reminder. To optimise participation in the face-to-face session in each PCT, we will contact the PCT director so that they decide the best date within a 4-month period. A pair of researchers will go to each PCT to deliver the face-to-face session.

#### Data management {19}

Clinical trial data will be entered electronically. Variables will be extracted from the SIDIAP before starting the training and quarterly during the 12 months after the start of the trial. The data of all patients with a new diagnosis of vertigo and dizziness in participating centres will also be collected, ensuring a sample size greater than necessary. The files will be safely stored in numerical order in one location for a period of 3 years after the end of the study. Only SIDIAP staff will be able to export these data.

#### Confidentiality {27}

The data will be anonymised, encrypted and collected by computerised extraction without the need to consult other data in the medical records. Only data of interest will be extracted.

The statistical code and datasets analysed during the current study will be available from the corresponding author on reasonable request.

#### Plans for collection, laboratory evaluation and storage of biological specimens for genetic or molecular analysis in this trial/future use {33}

Not applicable, this study does not involve the collection of biological samples. Not applicable due to the characteristics of the study.

## Statistical methods

### Statistical methods for primary and secondary outcomes {20a}

Data analyses will follow Consort Cluster recommendations (http://www.equator-network.org/reporting-guidelines/consort-cluster/), and intention-to-treat analysis will be used for comparisons between the groups. We will firstly analyse the baseline comparability of the two groups to verify homogeneity regarding study variables. Descriptive statistics will be performed for all baseline variables, using Student’s *t* or Mann-Whitney *U* test for quantitative variables, and chi-square or Fisher’s exact test for categorical variables.

The *t*-test will evaluate differences in outcome variables between the groups pre- and post-intervention. Logistic regression multivariate analysis will be performed to analyse the relationship between baseline variables of primary care centres and professionals, and outcome variables. Significance will be set at 5% for all analyses. Statistical software R (revised version 3.2.4) will be used.

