**Methods:**

To evaluate the effectiveness of blended training (online and face-to-face) on the diagnosis and management of vertigo to improve adherence of family doctors to clinical practice guidelines, we designed a community multicentre cluster-randomised open-label trial with an intervention (IG) and a control (GC) group of 10 primary care teams (PCT) each. Outcome variables will be ICD-10 diagnostic codes (proportion of nonspecific diagnoses such as dizziness and vertigo versus specific diagnoses such as BPPV, vestibular neuritis, and Menière’s disease); number of referrals to ENT or neurology specialists; prescription of antivertigo agents; and duration of sick leave due to vertigo. The baseline comparability of the two study groups will be analysed to ensure homogeneity. A description of all baseline variables will be performed. Student’s *t*-test will be used to evaluate the differences between the groups. Logistic regression multivariate analysis will be performed to study the relationship between baseline variables of professionals and centres with outcome variables.

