### Trial design {8}

To measure the effectiveness of the training in the IG, we designed a community multicentre cluster-randomised open-label trial, with the PCT as the allocation unit. The professionals of the PCT in the IG will receive training at the beginning of the study. PCT in the CG will be offered the training after study completion. Adherence to clinical practice guidelines will be measured during the year after completion of training in each PCT.

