## Methods: participants, interventions and outcomes (Fig. 1)

### Study setting {9}

The study setting is Metropolitana Sud Area – Catalan Institute of Health (ICS), which in 2016 had 56 PCT for a catchment population of 1,334,381 people, of which 1,042,920 had been visited during that same year. A random sample of 20 PCT will be chosen from the 56; 10 will be included in the IG, and 10 in the CG.

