#### Sample size {14}

To improve vertigo diagnostic codes, accepting an alpha risk of 0.05 and a beta risk < 0.2 in a two-sided test, a total of 356 patients are needed per group (IG and CG) to detect as statistically significant a difference of 30% and 40% in correct diagnoses (BPPV, vestibular neuritis, vestibular migraine and Menière’s disease) for the CG and IG, respectively, with no loss to follow-up anticipated (GRANMO calculator, Institut Municipal d’Investigació Mèdica, Barcelona, Spain, using the ARCSINUS approach). To evaluate the final sample size, we take into account that the intercluster correlation coefficient (ICC) most commonly used in cluster-randomised trials in PC is 0.05. This ICC translated to a size of 45 individuals (assuming 10 clusters per group) in the design is adjusted by 1.24, i.e. *n* = 712 × 1.24 = 884 (45 per centre).

Similarly, the comparison of expected variation proportions for the prescription of antivertigo agents is 58.21% and 48% for the CG and IG, respectively (374 per group before adjustment by design) and 20% and 10% for referrals to neurology and ENT (195 per group before adjustment for design). All proportion estimates are based on the results of the previously published study [20].

However, data from *all* patients with a new diagnosis of vertigo and dizziness during the study period (1 year after the intervention) in participating centres will be collected, ensuring a number greater than the sample calculation.

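### The t-test named for outcomes has no stated unit of analysis and no adjustment for PCT; run on patients, its type I error would be about 27% at the plan's own ICC and cluster size

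*Protocol article*

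**What the plan says.** The trial design section describes a "cluster-randomised open-label trial, with the PCT as the allocation unit". Study setting {9} adds that "10 will be included in the IG, and 10 in the CG". Sample size {14} recognises correlation within teams: it states that "the intercluster correlation coefficient (ICC) most commonly used in cluster-randomised trials in PC is 0.05" and inflates the patient count for it.

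The outcome analysis is fixed in Statistical methods for primary and secondary outcomes {20a}. A t-test "will evaluate differences in outcome variables between the groups pre- and post-intervention". The Abstract repeats this: Student's t-test "will be used to evaluate the differences between the groups". Section {20a} also plans a multivariable logistic regression relating baseline characteristics of centres and professionals to the outcomes.

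For neither method does the article name a PCT random effect, GEE, cluster-robust variance, PCT-level summary or degrees of freedom based on the number of teams. Clustering enters the analysis only through a commitment, in {20a} and again in {20c}, to the CONSORT extension for cluster trials. The article links that extension as a reporting guideline and draws no method from it.

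**The concern.** Patients of one team share doctors, coding habits and referral routes, so their outcomes are correlated. The sample size accepts this, but the named test does not visibly carry it through. If a t-test treats each patient as independent, it understates the standard error by the square root of the design effect, and p-values and confidence intervals are then too optimistic.

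Collecting more patients per team makes this worse, because the design effect grows with cluster size. The plan collects every new vertigo or dizziness patient in the participating centres, and Sample size {14} expects this to exceed the calculated number. The same problem affects the logistic regression. Its explanatory variables include centre-level characteristics, which are constant within a team.

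At stake is whether a significant result for the training can be taken at its nominal 5%.

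**Working it through.** **Inputs from the protocol article.** Unit of randomisation: "with the PCT as the allocation unit" (Trial design {8}). Teams: 10 per arm (Study setting {9}). Error rates: "accepting an alpha risk of 0.05 and a beta risk < 0.2 in a two-sided test". Target: "a difference of 30% and 40% in correct diagnoses". Also from Sample size {14}: ICC 0.05, 45 patients per PCT, inflation factor 1.24, and 356 per group before inflation.

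**Assumptions.** The article does not give the number of vertigo patients per PCT. I take 200 and 500 as illustrations. With 1,042,920 / 56 = 18,624 people visited per PCT in 2016, these are 1.1% and 2.7% of visited patients. I also vary the ICC, because 0.05 is given as a commonly used value and not as an estimate for this outcome.

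**The plan's own figure.** Arcsine method: n = 2 × [(z₀.₉₇₅ + z₀.₈₀) / (2·asin√0.30 − 2·asin√0.40)]² = 355.4, so 356 per group, as stated. Then 712 × 1.24 = 882.9, printed as 884, a small difference.

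**Design effect.** DE = 1 + (m − 1) × ICC. At the stated ICC and cluster size, DE = 1 + 44 × 0.05 = 3.20, not 1.24. A factor of 1.24 at 45 per PCT would need an ICC of 0.24 / 44 = 0.0055. That mismatch is a separate sample-size matter, so both values are carried below.

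**Type I error of a patient-level test that ignores PCT.** α = 2 × [1 − Φ(1.96 / √DE)]. For DE = 3.20: √3.20 = 1.79, 1.96 / 1.79 = 1.10, α = 27.3%.

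| ICC | Patients per PCT | DE | SE too small by factor | True type I error |
|---|---|---|---|---|
| 0.0055 (implied by 1.24) | 45 | 1.24 | 1.11 | 7.8% |
| 0.01 | 45 | 1.44 | 1.20 | 10.2% |
| 0.01 | 200 (assumed) | 2.99 | 1.73 | 25.7% |
| 0.05 | 45 | 3.20 | 1.79 | 27.3% |
| 0.05 | 200 (assumed) | 10.95 | 3.31 | 55.4% |
| 0.05 | 500 (assumed) | 25.95 | 5.09 | 70.0% |

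**Simulation check.** I simulated 20,000 trials per setting with no training effect (beta-binomial data, 10 against 10 teams, event rate 0.35). At ICC 0.05 the patient-level t-test rejected in 27.2%, 56.3% and 70.5% of trials for 45, 200 and 500 patients per PCT. A t-test on the 20 PCT proportions rejected in 4.7%, 5.2% and 5.0%. At ICC 0.01 the patient-level test rejected in 10.3%, 25.9% and 42.7%, and the PCT-level test in 5.1% throughout.

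**The case against.** The best defence is that the article never says the t-test is run on patients. Outcomes {12} defines several outcomes as aggregates: a ratio of specific to nonspecific codes, the share of a team's vertigo patients given an antivertigo drug, a referral percentage and a total of sick-leave days. A t-test suits team percentages at least as well as yes/no data from individuals. On that reading the named test is already valid. A sample size counted in patients does not rule this out, since cluster trials routinely count patients and then inflate. The analysis also commits to the cluster extension of CONSORT, and a fuller plan may exist.

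Much of this stands. A reader might infer that the plan definitely ignores clustering and that its false-positive rate is therefore several times 5%. The text does not support this: the unit is open, and every error rate above holds only for a patient-level analysis. Two further inferences also fail. Chi-square and Fisher's tests are named for baseline variables only, so they are not outcome tests here. The logistic regression is described as relating baseline variables to outcomes, not as the comparison between arms, and nothing says which form of it will be fitted.

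What does not stand is that nothing needs correcting. This is not a detail merely left to an analysis plan: the article names its outcome test twice, and a reporting guideline does not supply the unit or the variance for it. The patient-based sample size and the extraction of all patients leave the patient-level reading natural. Because {17a} makes even the data analysis open-label, an unstated unit could also be settled after the results are seen.

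**Conclusion.** The point holds in conditional form. In a trial randomised by PCT, the article names a t-test for the outcome comparison without its unit of analysis or any adjustment for PCT, and a logistic regression without a PCT term.

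If the t-test is run on patients, the true type I error at the plan's own ICC and cluster size is about 27%, more than five times nominal. The size depends strongly on both inputs: about 8% to 10% under the milder assumptions at 45 per PCT, and 55% to 70% at ICC 0.05 with the assumed larger clusters. A reader might conclude from the upper figures that a significant result is likely even with no training effect. That would need the larger clusters, whose size the documents do not give, as well as the full ICC. If the test is run on the 20 PCT summaries, the error is about 5% and only the wording is deficient.

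Under either reading {20a} has to change, because a valid test and a seriously anticonservative one both fit the present text.

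**What to change.** In {20a}, and in the Abstract to match, state the treatment comparison for the primary and all secondary outcomes as one of these:

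- a t-test, or an ANCOVA adjusting for the pre-intervention PCT value, on the 20 PCT-level summaries with at most 18 degrees of freedom; or
- a mixed model or GEE with arm as a fixed effect, PCT as the cluster and a small-sample correction, since there are only 20 clusters.

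Add a PCT random effect or a cluster-robust variance to the logistic regression, and report the estimated ICC for each outcome.

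The cost is a few sentences and a little more analysis code, with no change to conduct or data collection. Confidence intervals will be wider than from an unadjusted patient-level analysis, by a factor of about 1.79 at ICC 0.05 and 45 per PCT, before allowing for the fewer degrees of freedom.

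### The stated t-test comparison is not said to adjust for each PCT's own pre-intervention outcome, although that outcome is already being extracted

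*Protocol article*

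**What the plan says.** The Study setting section sets January to December 2021 as the pre-intervention period and January to December 2022 as the post-intervention period. Outcomes {12} takes SIDIAP data at baseline and over the following year for everyone assigned to the participating PCT. Data management {19} agrees: "Variables will be extracted from the SIDIAP before starting the training", and then quarterly. So each PCT will have its own earlier value of each routinely recorded outcome.

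Statistical methods {20a} gives baseline one explicit use: "We will firstly analyse the baseline comparability of the two groups to verify homogeneity regarding study variables". It then names a t-test for outcome differences between the groups before and after the intervention. It does not say whether each period is tested separately or the change is compared. The one regression is this: "Logistic regression multivariate analysis will be performed to analyse the relationship between baseline variables of primary care centres and professionals, and outcome variables". Study arm and prior outcome are not among its named terms. Section {20b} anticipates no additional analyses, and the abstract describes the same set of methods.

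**The concern.** With 10 PCT per arm and many patients in each, variation between PCT dominates the error of the treatment comparison. Adding patients within a PCT hardly reduces it. A PCT's earlier proportion of specific diagnoses is a natural predictor of its later one, and adjusting for it removes part of exactly that variation.

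Sequence generation {16a} describes simple random assignment with no stratification or matching, so chance differences in baseline coding habits are to be expected. A homogeneity test can reveal such a difference but neither prevents nor corrects it. At stake are the precision of the primary comparison and how readily a result can be explained by which PCT fell into which arm.

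**Working it through.** **Inputs from Sample size {14}**
- Error rates: "accepting an alpha risk of 0.05 and a beta risk < 0.2 in a two-sided test".
- Effect: "a difference of 30% and 40% in correct diagnoses", control and intervention respectively.
- Clustering: "the intercluster correlation coefficient (ICC) most commonly used in cluster-randomised trials in PC is 0.05".
- 10 PCT per arm, 45 patients per PCT in the calculation. All new vertigo and dizziness diagnoses will in fact be collected, and the number per PCT is not given.

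**Assumptions.** Patients per PCT m = 45, 200 or 1000. PCT-level pre/post correlation r = 0.3, 0.5, 0.7 or 0.8. The comparison is taken at PCT level, so that clustering is respected.

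**1. The plan's own figure.** Arcsine method: h = 2·asin(√0.4) − 2·asin(√0.3) = 0.2102. n = 2(1.960 + 0.842)²/h² = 355.4, so 356 per group. This reproduces.

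**2. Design effect.** 1 + (m − 1)·ICC = 1 + 44 × 0.05 = 3.20, not the stated 1.24. The figure 1.24 would need an ICC of 0.24/44 ≈ 0.0055. This is a separate matter. It enters here only because it decides how much variation between PCT there is to remove.

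**3. Unadjusted power.** SE² = [0.3 × 0.7 + 0.4 × 0.6] × [1 + (m − 1) × 0.05]/(10m), noncentral t on 18 df.
- m = 45: SE² = 0.45 × 3.20/450 = 0.00320, SE = 0.0566, power 39%.
- m = 200: SE² = 0.45 × 10.95/2000 = 0.00246, SE = 0.0496, power 48%.
- m = 1000: SE² = 0.45 × 50.95/10000 = 0.00229, SE = 0.0479, power 51%.

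Collecting every patient therefore does not reach 80% at this ICC.

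**4. Adjusting for the PCT's baseline value.** The variance is multiplied by 1 − r², on 17 df. A t-test on change multiplies it by 2(1 − r), on 18 df.

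| r | 1 − r² | 2(1 − r) | Adjusted power, m = 200 | Adjusted power, m = 1000 |
|---|---|---|---|---|
| 0.3 | 0.91 | 1.4 | 51% | 54% |
| 0.5 | 0.75 | 1.0 | 59% | 62% |
| 0.7 | 0.51 | 0.6 | 76% | 79% |
| 0.8 | 0.36 | 0.4 | 89% | 91% |

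Since 1 − r² = (1 − r)(1 + r), it is below 2(1 − r) for every r < 1. Below r = 0.5 the change factor exceeds 1. At r = 0.3 and m = 200, power is 36% on change, 48% unadjusted and 51% adjusted.

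**5. Limits on r.** Sampling error within PCT caps r at m·ICC/[1 + (m − 1)·ICC]. At m = 45 and ICC 0.05 the cap is 2.25/3.20 = 0.70, so r = 0.8 cannot occur there. Adjusted power at m = 45 is 42%, 49% and 65% for r = 0.3, 0.5 and 0.7.

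**6. If the ICC were 0.0055.** At m = 45 unadjusted power is 76.5%. Even if the underlying PCT levels correlate at 0.9 across years, r is only 0.18 and adjusted power 77.6%. At m = 200 unadjusted power is already 99%.

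**7. Chance baseline imbalance.** The SD of the arm difference in mean baseline proportion is √(2 × 0.3 × 0.7 × [1 + (m − 1) × 0.05]/(10m)). This gives 5.5 points at m = 45, 4.8 at 200 and 4.6 at 1000, about half the 10-point target effect.

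**The case against.** A reader might infer that the plan never uses baseline in the treatment comparison, or uses it only for the homogeneity check. The text does not support so firm a reading. The t-test sentence can mean a comparison of pre-to-post change, which does use baseline. The centre-level baseline variables in the logistic model could also include prior outcome rates. What stands is that adjustment of the arm effect is not stated and the quantity tested is unclear. Step 4 shows that adjustment is more efficient under either reading.

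A reader might also call this the largest gain available. That cannot be shown. The documents give no r, and at r = 0.3 the gain is about 3 points. PCT were focused on COVID-19, so 2021 may predict 2022 poorly. Retaining all 15 randomised PCT per arm, were they eligible, would give about 70% unadjusted power at m = 1000, more than adjustment with 10 per arm at r = 0.5. Normal-approximation power figures come out higher but are too generous for 20 clusters.

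Leaving out baseline adjustment does not in itself bias a randomised comparison, and the choice of covariates is often left to an analysis plan. Both points are fair and keep this a matter of precision and clarity. But the article does state the treatment comparison, so what it states can be judged.

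Finally, nothing says that the homogeneity tests will select covariates. That criticism would have no basis in the text.

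**Conclusion.** The point holds in limited form. The protocol fixes a t-test for the arm comparison, leaves unclear what it compares, and does not state adjustment for a pre-intervention outcome that it already plans to extract. At its own ICC of 0.05 with 10 PCT per arm, adjustment raises power at every correlation examined, after paying for the lost degree of freedom. The gain is about 3 points at r = 0.3, 11 to 12 at r = 0.5, 28 at r = 0.7 and 40 to 41 at r = 0.8, for 200 to 1000 patients per PCT. These sizes rest on assumed r and m and on the stated ICC, and they largely vanish at the ICC that 1.24 implies. The change is worth making because it is cheap and improves on either reading of the current text, but a particular power should not be promised from it.

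**What to change.** In Statistical methods {20a}, state the quantity compared. Make the primary estimate the between-arm effect from a cluster-level or mixed model adjusted for each PCT's pre-intervention proportion of specific diagnoses. Treat each secondary outcome in the same way, with its own pre-intervention PCT value. Name these covariates in advance.

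Close the baseline window before intervention teams gain access to the course. The Participant timeline places that access in November and December 2021, inside the period labelled pre-intervention; January to October 2021 would avoid the overlap.

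The cost is one degree of freedom (17 instead of 18 in a PCT-level analysis) and a slightly shorter baseline window. The source data are already due to be extracted.
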